**Figure 2 BMJOPEN2015008586F2:**
[figure not shown]
DART study flowchart. AUDIT-C, the Alcohol Use Disorders Identification Test; DART, The Dental Alcohol Reduction Trial.

## Outcomes

We will measure recruitment and retention rates as well as practicality of engagement with dental practices, fidelity of delivery of the intervention and general acceptability of the study procedures from screening to follow-up. In addition, we will also assess if outcome measures proposed for the main trial could successfully be collected. The proposed primary outcome of the full trial is the score on the full AUDIT questionnaire, with a cut-off of 8 or more as used in the SIPS programme.^23^ Proposed secondary outcomes include mean weekly units of alcohol consumed during the previous 90 days using the Form 90^27^ average drinks (8 mg of pure ethanol) per day, health-related quality of life measure using EQ-5D^26^ for the economic evaluation calculations, and questions relating to satisfaction with dental services taken from the Adult Dental Health Survey 2009.^13^ Rates of data completeness for the proposed outcomes will also be evaluated.

## Sample size

For feasibility studies a detailed sample size calculation is neither appropriate nor necessary. The primary aim of conducting feasibility trials is to provide data to inform power calculations for a future larger scale trial.^30^

Based on pragmatic considerations it was estimated that 12 dental practices were required with a sample of 240 participants at baseline—20 participants per practice. Assuming a 30% drop out rate this would give a sample of 168 participants at the 6 months follow-up. This figure was deemed to be reasonable as the average dental practice has approximately 1500 adult patients of whom approximately 25% were drinking at higher risk levels^15^ and if 60% of the patients screened agreed to participate.

No published studies have reported the effect of brief advice provided in general dental practice. The variance in the proposed primary outcome for the definitive trial (AUDIT score at 6 months) will be used in conjunction with recruitment and follow-up rates as well as an estimate of the intraclass correlation coefficient (and 95% CIs) in order to calculate the sample size for the definitive trial.

## Patient and public involvement

To ensure that the study was relevant and informed by patient experience, a dental patient research forum was established in one of the dental practices involved in the study. The principal dentist invited a diverse mix of dental patients to join the forum. Semistructured discussions took place with the forum members. These discussions were facilitated by the patient and public involvement co-investigator (CG) and members of the study team. The forum was consulted on a variety of practical aspects of the study, such as the design of recruitment materials and data collection questionnaires, the best ways to introduce the study to potential participants, suggestions on retention of the study sample and effective follow-up methods. The group also assisted with piloting the data collection questionnaires once they were finalised.

## Data monitoring procedures

The research team developed a comprehensive monitoring system with monthly visits to the dental practices to collect the screening and baseline questionnaires and to ascertain if recruitment and data collection were going well. Visit checklists were designed and completed at each visit and feedback emails were sent when deemed useful for the practitioners.

## Process evaluation

The process evaluation will consist of a mixed methodology using both qualitative and quantitative methods. This will include an assessment of the recruitment procedures, satisfaction among participating dental patients and dental teams, and intervention fidelity.

### Intervention fidelity

All dentists at the intervention practices were asked to complete a fidelity form for each patient who received the brief intervention to ensure that the intervention was delivered consistently. The form was based on a checklist used in a previous trial,^31^ covered all components of the brief advice delivered, and included a question asking how long it took to deliver the intervention.

### Interviews with patients and dental professionals

Face to face individual interviews will be held in the intervention and control dental practices to gain an understanding of the dental professionals’ experience and views of the study. Dentists and reception staff who were directly involved with the recruitment and data collection process will be interviewed by the research team on an individual basis. The discussions with the intervention practices will assess views on the recruitment procedures, value and relevance of the alcohol brief advice training, the appropriateness of delivering advice on alcohol in the dental practice and overall perceptions surrounding participation in research. In the control practices, the discussions will focus on the study protocol procedures namely the challenges and facilitators in recruiting dental patients for the study and the data collection process. In addition, dentists in the control arm will be asked if they would find the training for delivering alcohol advice relevant and useful to them.

The experience of participants will also be evaluated through individual telephone interviews and will focus on their experiences of the study (the recruitment and data collection process, their thoughts on the delivery of the alcohol brief advice by the dentist, whether the advice had an impact on their alcohol consumption) and general perceptions around participating in research. Members of the research team will also be interviewed one-to-one by an external interviewer, discussions surrounding recruitment of dental practices, training of dental teams and general perceptions of the organisation of the study will be carried out.

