## Aims and objectives

The Dental Alcohol Reduction Trial (DART) study aimed to assess the feasibility and acceptability of screening for alcohol misuse and delivering brief advice to patients attending NHS general dental practices in North London.

The study objectives were:
To explore the views of dental professionals and dental patients on the relevance and importance of alcohol misuse to oral health, as well as the acceptability of screening and providing brief alcohol advice in general dental settings.To develop and evaluate a brief alcohol advice intervention tailored for use in NHS general dental practices and to assess through a process evaluation the feasibility and acceptability of the intervention to patients and dental professionals.To assess the feasibility of the main trial methodology including the use of a screening tool, subject recruitment and retention, and data collection procedures including economic evaluation to inform the future design of a definitive randomised controlled trial.

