### Screening

From our exploratory work, it was ascertained that compared to the M-SASQ and FAST alcohol screening questionnaires, the AUDIT-C questionnaire^23^ was considered preferable by dental professionals and patients in terms of the time needed to complete the instrument and the nature of the questions included. The AUDIT-C is an effective and practical screening tool for detecting alcohol misuse in primary care settings.^24^
^25^ To mask the focus on alcohol particularly for the participants in the control group, the screening questionnaire also included some more general lifestyle questions on diet and smoking, in addition to the AUDIT-C alcohol questions.

Patients who expressed an interest in participating in the study completed the screening questionnaire, which was then given to the dentist in order to ascertain eligibility for the study. A score of 5 or above in the AUDIT-C questions indicates drinking levels above the current recommendations and therefore eligibility to enter the study.^12^ After eligibility was ascertained, the dentist introduced the study. In the control arm the study was introduced as a lifestyle survey with no specific mention of alcohol. In the intervention arm, the study was introduced as a lifestyle survey but with a focus on alcohol in particular.

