## Follow-up measures

Six months after the completion of baseline measures, all participants will be contacted via telephone by a researcher masked to the participant's allocation status. The full AUDIT tool will be administered.^24^ Alcohol consumption in the last 90 days will also be collected using the Form 90.^27^ This validated alcohol consumption tool provides a detailed day-by-day account of alcohol use in the 90 days prior to the interview. As in baseline, the health-related quality of life EQ-5D measure will also be completed^26^ along with a short patient satisfaction questionnaire on services received at the dental practice.

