## Discussion

Alcohol misuse remains a major health and social problem in the UK affecting a significant proportion of the population. Excessive alcohol consumption adversely affects oral health in a variety of ways, but currently most dentists do not ask their patients about their alcohol intake or provide any advice to those that require support. Indeed, many health professionals lack the necessary knowledge and confidence to discuss alcohol misuse with their patients.^32^ Previous studies have shown that dentists were also concerned about their lack of knowledge in this field and worried that they might alienate their patients by raising the topic of alcohol.^20^ Dentists working in primary care are, however, in an ideal position to offer brief advice to their patients, many of whom will not have contact with any other health professional. Despite this opportunity very few studies have developed and evaluated alcohol brief advice interventions in primary dental care settings.

This paper has described the study methodology and intervention design for an alcohol screening and brief advice intervention delivered in NHS dental practices in North London. The comprehensive feasibility study will provide detailed insights into the development, implementation and evaluation of the alcohol intervention which will inform the design of a future definitive trial. Findings from the initial exploratory phase of the study will help ensure that the intervention training programme and resources are tailored to the needs and circumstances of NHS dental professionals.

Furthermore, the feasibility trial will explore the logistics and practicality of delivering brief advice to dental patients in a NHS dental setting. The planned process evaluation will determine the acceptability of the intervention to dental professionals and patients. These implementation and feasibility issues will be explored in depth as they will likely influence uptake of this approach in primary dental care. The comprehensive methodology of this study will provide useful data on this important and under researched topic and provide evidence which will inform primary dental care practice in and outside of the UK.

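### In the trial phase, acceptability is asked only of enrolled patients and directly involved staff, so the finding is likely to lean towards acceptable

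*Protocol article*

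**What the plan says.** Under Aims and objectives, the study "aimed to assess the feasibility and acceptability of screening for alcohol misuse and delivering brief advice to patients attending NHS general dental practices". The Outcomes section extends acceptability to every study procedure, from screening through to follow-up. The Discussion says where the answer on the intervention will come from: "The planned process evaluation will determine the acceptability of the intervention to dental professionals and patients".

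The article also says who will be asked:

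- **Scope.** The Process evaluation section covers "satisfaction among participating dental patients and dental teams, and intervention fidelity".
- **Staff.** Under Interviews with patients and dental professionals, "Dentists and reception staff who were directly involved with the recruitment and data collection process will be interviewed by the research team". This applies in both arms.
- **Patients.** The same section says "The experience of participants will also be evaluated through individual telephone interviews". At the six-month telephone contact, participants also complete a "short patient satisfaction questionnaire on services received at the dental practice" (Follow-up measures).
- **How a patient becomes a participant.** Under Screening, "Patients who expressed an interest in participating in the study completed the screening questionnaire". They then had to score 5 or above on the AUDIT-C and give written consent.

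**The concern.** A patient is asked for a view only after accepting screening and then accepting the trial. A staff member is asked only after being active in recruitment and data collection. Being asked therefore depends on having accepted, and acceptance is the thing being judged.

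This matters more here because the article itself names the likely barrier. The Introduction reports that dentists are reluctant to raise alcohol with patients, and the Discussion reports their worry about alienating them. A dentist who disliked the task, or a patient put off by it, is less likely than others to be within the group that is asked.

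What is at stake is the headline statement on acceptability. If it is worded for all attending patients and all trained dentists, it goes further than the people who supplied it, and it would carry that gap into the design of the definitive trial.

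**Working it through.** **1. The plan's own figures (Sample size).** 12 practices × 20 patients = 240 at baseline. 240 × (1 − 0.30) = 168 at six months. Both reproduce.

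**2. Who is asked in the trial phase.**

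| Group | Route to their views |
|---|---|
| Patients who refuse screening | none described |
| Patients who screen negative | none described |
| Patients who screen positive and decline | none described |
| Enrolled patients | telephone interview; satisfaction questionnaire at six months, on dental services rather than on screening |
| Staff directly involved in recruitment and data collection | face-to-face interview |
| Trained intervention dentists not involved in recruitment | not clearly included |

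**3. How many eligible patients go unheard.** The input is the 60% agreement in the Sample size section. I read it as agreement among screen-positive patients; this is an assumption, since the sentence speaks of patients screened.

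- Eligible: 240 / 0.60 = 400.
- Decline: 400 − 240 = 160, or 40% of the eligible.
- If only patients retained at six months are reached: 168 / 400 = 42% of the eligible are heard.

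The 25% prevalence does not enter these three figures. If it held among those screened, screening would reach 400 / 0.25 = 1,600 patients, of whom 1,200 would be negative. That total is only implied. The article says that some practices targeted patients they knew, so the positive rate among those screened need not be 25%.

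**4. What the gap could do.** Let p be acceptability among participants and d acceptability among eligible decliners. Acceptability among all eligible patients is 0.6p + 0.4d, so the overstatement is 0.4(p − d). The document gives neither p nor d. Assuming p = 90%:

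| d (assumed) | All eligible | Overstatement (points) |
|---|---|---|
| 90% | 90% | 0 |
| 70% | 82% | 8 |
| 50% | 74% | 16 |
| 30% | 66% | 24 |
| 10% | 58% | 32 |

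The table shows direction and sensitivity only. It does not predict a result, because the plan reports no acceptability percentage: the interviews go to thematic analysis.

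**The case against.** The strongest reply is that acceptability has several sources, and that interviewing participants and involved staff is normal in a process evaluation.

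- **Focus groups.** Two groups of professionals and three of patients discussed the acceptability of alcohol screening and advice before the trial. A reader might infer that nobody outside the trial is ever asked; that is wrong for the study as a whole. But those were prospective views used to design the intervention. They cannot report reactions to screening or advice as delivered.
- **Uptake.** Planned data analysis uses recruitment rates and numbers screened to inform acceptability, and fidelity forms are requested for each advised patient. Refusal and non-delivery can therefore be counted. Counts do not separate dislike of the alcohol questions from lack of time or reluctance to join research.
- **Staff wording.** A reader might infer that dentists who were trained but recruited nobody are excluded. The text does not say so: a dentist who tried and failed could count as directly involved. What stands is that the wording leaves this open.
- **Critical content.** Control interviews cover challenges as well as facilitators, and intervention interviews ask whether giving alcohol advice in the practice is appropriate. This lets criticism in, but only from those interviewed.
- **Condensation.** Sampling details often sit in a fuller protocol. Here, though, the article positively states who will be interviewed, and states it restrictively.

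**Conclusion.** The point holds for the trial phase and should be acted on. The stated aim covers screening and advice among attending patients, while the views collected come from those who accepted both screening and trial entry and from staff active in the study. The finding is likely to lean towards acceptable.

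A reader might go further and say that it will be biased, or by how much. The documents support neither. If decliners think as participants do, there is no bias, and their views are not given. The one size that can be stated is about 160 of 400 eligible patients declining unheard, resting on the 60% agreement as read above. Screen-negative patients and those who refuse screening come on top, in numbers that the document does not fix.

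A reader might also infer that the decision to proceed is compromised. It is not directly affected: that rule uses recruitment (85%), follow-up (75%) and receipt of advice (60%), and no interview finding.

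**What to change.** 1. **Staff interviews.** In the interview section, invite all dentists trained at the intervention practices, including any who recruited or advised nobody. The section on training and support says that all intervention dentists attended the course, so the list is known, and the interviews are still described in the future tense.
2. **Patient conclusion.** State that acceptability to patients is concluded only for those who took part. Report it beside the numbers approached, screened, eligible and declining.
3. **Only if screening is still open.** Add one neutrally worded comfort item to the screening questionnaire in both arms, without singling out alcohol, so that the control arm's masking is kept. Report it as comfort with the lifestyle questions among screened patients. It measures reaction to a mixed diet, smoking and alcohol form, and it still misses those who refuse screening. Recruitment began in May 2014, so it is probably too late.

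The cost is a few extra short interviews by the existing team and a narrower, possibly less favourable, conclusion. No planned sample size or progression criterion changes.

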## Planned data analysis

We will assess key feasibility parameters, such as recruitment and retention rates, number of participants screened in order to assess eligibility, the practicalities of screening and delivering the intervention in dental settings, in order to inform the acceptability of the study procedures in both patients and dental professionals. The study instruments will be evaluated in terms of ease of administration as well as acceptability by participants in order to inform their suitability for the main trial. Descriptive analysis of the proposed main outcome measure (AUDIT score) will provide a SD which will be subsequently used in the sample size calculation for the definitive trial.

The process evaluation interviews with dentists, dental teams, dental patients and members of the research team involved in the study will be transcribed and coded, classified and organised into main themes using thematic analysis.

A decision to process to the full scale study will be based on recruitment of at least 85% of the planned sample within the allocated time, completion of primary outcome follow-up interviews with no less than 75% of participants and receipt of brief advice by at least 60% of those randomised to the intervention arm.

## Discussion

Alcohol misuse remains a major health and social problem in the UK affecting a significant proportion of the population. Excessive alcohol consumption adversely affects oral health in a variety of ways, but currently most dentists do not ask their patients about their alcohol intake or provide any advice to those that require support. Indeed, many health professionals lack the necessary knowledge and confidence to discuss alcohol misuse with their patients.^32^ Previous studies have shown that dentists were also concerned about their lack of knowledge in this field and worried that they might alienate their patients by raising the topic of alcohol.^20^ Dentists working in primary care are, however, in an ideal position to offer brief advice to their patients, many of whom will not have contact with any other health professional. Despite this opportunity very few studies have developed and evaluated alcohol brief advice interventions in primary dental care settings.

This paper has described the study methodology and intervention design for an alcohol screening and brief advice intervention delivered in NHS dental practices in North London. The comprehensive feasibility study will provide detailed insights into the development, implementation and evaluation of the alcohol intervention which will inform the design of a future definitive trial. Findings from the initial exploratory phase of the study will help ensure that the intervention training programme and resources are tailored to the needs and circumstances of NHS dental professionals.

Furthermore, the feasibility trial will explore the logistics and practicality of delivering brief advice to dental patients in a NHS dental setting. The planned process evaluation will determine the acceptability of the intervention to dental professionals and patients. These implementation and feasibility issues will be explored in depth as they will likely influence uptake of this approach in primary dental care. The comprehensive methodology of this study will provide useful data on this important and under researched topic and provide evidence which will inform primary dental care practice in and outside of the UK.
